### Data monitoring, auditing, and interim analysis

Data monitoring and auditing will be conducted by the funding agency annually. An interim analysis will be performed by an independent statistician when half of the patients have been randomized. The trial will be stopped if one treatment is found to be statistically more beneficial or harmful than the other.

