After completing an initial assessment and signing an informed consent form, participants will be randomized with 1:1 ratio into two groups: autologous blood marker group and intraoperative colonoscopy group. The data manager, who will not be involved in eligibility assessment and recruitment of patients, will perform the randomization with a list of randomly ordered treatment identifiers generated by a permuted block design using SAS (version 9.1; SAS Institute Inc.). Although it will not be feasible to blind the surgeons and participants, the researcher performing the statistical analyses will be blinded to the patient group allocation.

This protocol and the informed consent forms have been reviewed and approved by Shanghai East Hospital and Institute Ethics Review Committee. We will obtain a new approval from the Committee if any amendments are made to the protocol or the informed consent form that may have an impact on the conduct of the study or potential benefit of the patient. A signed consent must be obtained from every participant in the ancillary study, if the data collection/request is not covered in the original informed consent process for the main clinical trial. The study has been registered in Clinical-Trial.gov (NCT05597384).

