### Sample size and statistical analysis

The primary objective of this study is to identify non-inferiority of autologous blood tattooing versus intraoperative colonoscopy group. Based on our current experience and previous studies which reported the rates of successful visualization, success rates of 99 and 95% were assumed for the intraoperative colonoscopy group and the autologous blood group, respectively. With settings of 80% power, 5% significance level, and non-inferiority margin of 10%, sample sizes of 110 patients in each group will be required.

Continuous variable will be presented as mean and SD if normally distributed, or as median and range otherwise. The differences between the groups were assessed using the t-test, the Mann-Whitney test, Fisher’s exact test, or the χ2 test, as appropriate. Multivariate analysis to assess the impact of potential con- founding factors (sex, age, body mass index, endoscopist, tumor location [colon vs. rectum], clinical tumor stage [≥ T2 vs. T1 or scars]) on invisible tattoo will be performed by using a logistic regression model. All tests will be two-sided with a significance level of *P* < 0.05. All statistical analyses will be carried out using SPSS software package (version 22.0; SPSS Inc.).

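### The binding half-way stopping rule tests for an ordinary difference at P < 0.05 and ignores the 10-point non-inferiority margin

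*Protocol article*

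**What the plan says.** **Interim analysis** (Protocol article, Data monitoring, auditing, and interim analysis). There is one look: "An interim analysis will be performed by an independent statistician when half of the patients have been randomized". The consequence is mandatory: "The trial will be stopped if one treatment is found to be statistically more beneficial or harmful than the other". The section names no endpoint, test or boundary, and it does not refer to the margin.

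**Significance level** (Sample size and statistical analysis). "All tests will be two-sided with a significance level of" P < 0.05, with no exception for the interim. The between-group tests listed, including Fisher's exact test and chi-squared as appropriate, all test for a difference.

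**Question and design assumptions** (same section). "The primary objective of this study is to identify non-inferiority of autologous blood tattooing versus intraoperative colonoscopy group". The planning values are "success rates of 99 and 95% were assumed for the intraoperative colonoscopy group and the autologous blood group, respectively". The settings are "With settings of 80% power, 5% significance level, and non-inferiority margin of 10" percent, from which "sample sizes of 110 patients in each group will be required".

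**Rates for blood in earlier work** (Discussion). Retrospective studies reported effective rates of 90.9% to 92.2%.

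**Safety** (Secondary outcomes). Tattoo-related events are evaluated in the blood group. Surgical complications are evaluated in both groups and graded by Clavien-Dindo.

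**The concern.** A non-inferiority trial asks whether blood is worse than colonoscopy by more than 10 points. The interim rule asks whether the arms differ at all. The design assumes a true 4-point deficit for blood and would still call blood non-inferior. A statistically significant deficit can therefore arise when the trial's hypothesis is true, and the rule would then close the trial.

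What is at stake is a trial stopped at half size with a confidence interval that lies on both sides of the margin, so that neither non-inferiority nor its absence is shown. A second issue is that two looks at the same 5% level give a superiority or harm claim more than a 5% chance of being false.

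**Working it through.** **Inputs.** Planned rates 99% (colonoscopy) and 95% (blood), margin 10 points, 110 per arm, 1:1 allocation, one look at half of the 220 patients, two-sided P < 0.05. Assumed here: exactly 55 per arm at the look, all outcomes known, no dropout, and localization accuracy as the endpoint compared.

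**1. The plan's own sample size.** n per arm = (z₁₋α + z₀.₈₀)² × [0.99×0.01 + 0.95×0.05] / (0.10 − 0.04)².
- One-sided 5%: (1.645 + 0.842)² × 0.0574 / 0.0036 = 98.6, so 99.
- One-sided 2.5%: (1.960 + 0.842)² × 0.0574 / 0.0036 = 125.1, so 126.

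Neither gives 110. A 10% dropout allowance on 99 would (99 / 0.9 = 110), but none is stated. That is a separate matter; the figures below take 110 as given.

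**2. Chance of a half-way stop against blood.** Sum the product of the two binomial probabilities (n = 55 each) over all outcomes where colonoscopy is better and P < 0.05.

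| True rates (colonoscopy / blood) | Fisher | Uncorrected chi-squared |
|---|---|---|
| 99 / 95 (planned) | 3.4% | 17.7% |
| 99 / 92.2 | 16.8% | 41.1% |
| 99 / 90.9 | 26.3% | 51.6% |

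In every row the true deficit (4, 6.8 or 8.1 points) is inside the margin. At 99/95 a stop in favour of blood has a probability of about one in a million with Fisher.

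**3. What a stop looks like.**
- *55/55 vs 51/55.* Chi-squared = 4² × 110 / (4 × 106) = 4.15, P = 0.042: stop. Fisher P = 0.118: continue. The Newcombe 95% interval for blood minus colonoscopy is −17.3 to +0.6 points.
- *55/55 vs 49/55.* With no control failures, six blood failures are the fewest that trigger Fisher (P = 0.027). The Wilson limits are 93.5% to 100% for 55/55 and 78.2% to 94.9% for 49/55. The observed difference is −10.9 points. The Newcombe lower limit is −10.9 − (89.1 − 78.2) = −21.8. The upper limit is −10.9 + √[(94.9 − 89.1)² + (100 − 93.5)²] = −2.2.

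Both intervals contain −10, so non-inferiority is unresolved when the trial closes.

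**4. Effect on showing non-inferiority at 99/95** (unpooled Wald limit at 110 per arm, exact enumeration).
- With the chi-squared rule, power falls from 72.8% to 66.9% (one-sided 2.5%) or from 78.2% to 71.1% (one-sided 5%).
- With the Fisher rule, it falls by 0.3 points or less.

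**5. Error rates.**
- *Superiority or harm claim.* With correlation √(55/110) = 0.707 between looks, 1 − P(|Z₁| < 1.96, |Z₂| < 1.96) = 8.3%. By exact enumeration with chi-squared, the error rises from 4.6% to 7.7% when both rates are 95%, and from 1.7% to 1.8% when both are 99%.
- *False non-inferiority claim.* At 99/89, on the margin, the chi-squared rule lowers it from 4.8% to 4.2% (one-sided 2.5% limit) or from 6.9% to 5.8% (one-sided 5% limit). Values above nominal come from the Wald limit at high rates, not from the interim look.

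**The case against.** **The likely test is Fisher's, so the chance of a stop is small.** At 55 per arm and 99/95, about 3.3 failures are expected in total (0.55 + 2.75), or about 1.7 per arm. The usual choice is then Fisher, which gives 3.4% and a negligible loss of power. Its smallest trigger with no control failures is an observed deficit of 10.9 points, just past the margin. This stands, and it is why the Fisher figures lead. It does not remove the defect: the interval at that trigger still contains −10, the chance rises to about 17% at a rate the protocol cites, and the text leaves the choice of test open for a binding decision.

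**The article is condensed and a boundary may exist elsewhere.** That the rule is unadjusted is inferred from two sections read together. But the article states a stopping criterion and a level for all tests, and any other document would have to override both.

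**Stronger readings a reader might infer, which the documents do not support:**
- *That the rule inflates the trial's primary error rate.* The 8.3% belongs to a test of no difference. False non-inferiority claims fall slightly, because stops against blood remove some of them.
- *That a significant result for colonoscopy is to be expected.* A true difference is assumed; a significant one at this look has a probability of 3% to 18% under the plan.
- *That the rule has nothing to do with the trial's question.* It may use the same outcome; what it lacks is the margin.
- *That harm can be found only against blood.* Tattoo-related events are assessed only in that arm, but surgical complications are evaluated in both, so a two-arm comparison is available.

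**Conclusion.** The concern holds in this form. Followed as written, a mandatory rule can end a non-inferiority trial on a difference that its margin permits. The chance is about 3% (Fisher) to 18% (uncorrected chi-squared) at the planned rates, and 17% to 41% if blood is 92.2%. The added error, about 8.3% by normal theory and less with exact calculation at these high rates, concerns only a superiority or harm claim. The harm to the primary question is a wrongful stop and lost power.

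The result assumes 55 per arm with complete outcomes, accuracy as the endpoint compared, and P < 0.05 applied at the interim because it is the only level given. It should be corrected before the interim look, since the rule leaves no discretion once triggered.

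**What to change.** Amend the interim section to:
1. Remove the stop for a statistically more beneficial treatment.
2. Tie any stop on localization accuracy to the margin, for example only if the confidence interval for blood minus colonoscopy lies wholly below −10 points.
3. Keep a separate safety comparison, based on events recorded in both arms, at a stringent prespecified level. Examples are Haybittle-Peto (interim P < 0.001, final P < 0.05, overall 5.02%) or O'Brien-Fleming (interim P < 0.0052, final P < 0.0480).
4. Name the interim endpoint and the test.
5. State that non-inferiority will not be claimed early, so the final test keeps its level.

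Tightening the level alone would not be enough. At 99/95 an O'Brien-Fleming interim level cuts the chance of a stop against blood from 17.7% to 0.35% (chi-squared) or from 3.4% to 0.09% (Fisher), but the criterion would still ignore the margin.

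The cost is a change of wording and a lower chance of stopping early. No extra patients are needed.

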### Adverse events

Adverse events are any unfavourable or unintended events that affect patients on study, regardless of the relevance to the treatment. Any adverse events will be recorded in detail on the CRF regarding its occurrence time, duration, relevance to the treatment, stopping or continuing of the treatment, etc. Events are defined as serious adverse events if leading to death, prolongation of hospitalization, permanent or severe disability, teratogenesis or carcinagensis, and significant clinical sequela [15]. The occurrence of serious adverse events will be reported to Shanghai East Hospital and Institute Ethics Review Committee within 24 h of the initial discovery.

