### Intervention

All patients will receive localization and surgery within 1 week after randomization. Endoscopic tattooing with autologous blood and intraoperative colonoscopy will be performed by two experienced endoscopists who has more than thousands of cases colonoscopies and more than 200 cases of endoscopic mucosal resection or endoscopic submucosal dissection.

For patients who will enroll in autologous blood group, the tattooing will be performed at 24–48 hours before the surgery. When the lesion is identified by endoscopy, the patient’s peripheral venous blood will be collected using a 10 ml simple syringe without heparin preparation. Immediately after blood sampling, 2–3 ml of autologous blood will be injected submucosally at the distal side and proximal side of the lesion (about 2 cm below and above the border of the lesion) using a conventional endoscopic needle without submucosal injection of normal saline. The tattooing with autologous blood will consider to be invisible if both distal and proximal spots was not identified. For those receiving autologous blood localization, the case will be applied intraoperative colonoscopy if the autologous blood tattoo will not be identified or inaccurate in the laparoscopic colectomy.

For patients who will enroll in intraoperative colonoscopy group, the patient will be placed in the modified lithotomy position under general anesthesia with endotracheal intubation. The legs will be opened and positioned in padded stirrups to facilitate the insertion and manipulation of the colonoscope during the operation. After routine laparoscopic exploration, CO_2_-insufflated intraoperative colonoscopy will be performed using a flexible videocolonoscope. Upstream small bowel clamping will be applied before intraoperative colonoscopy. During intraoperative colonoscopy, CO_2_ pneumoperitoneum will be maintained by the insufflator so that the laparoscope could guide the colonoscope effectively.

After lesion will be identified, a standard laparoscopic colectomy will be performed by two experienced surgeons who has more than 20 years of experience in colorectal surgery with more than 200 cases per year for all enrolled patients. All abdominal operation of laparoscopy will be videotaped. Anastomosis will be performed using the instrumental method. The specimen will be pulled out through a small median incision under the xiphoid (about 3–8 cm).

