For those receiving laparoscopic colectomy, the case will be required to be converted to open surgery if one of the following happens: severe or life-threatening intraoperative complications such as intra-abdominal massive haemorrhage, severe organ damage, or other technical or instrumental factors that require a conversion to open surgery.

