#### Secondary outcomes

The secondary endpoint, which is adverse events related to endoscopic tattooing, such as perforation, abscess formation, peritonitis, post-tattoo fever, post-tattoo abdominal pain, and intraperitoneal spillage of tattooing agent, will be evaluated in autologous blood group. Surgery related complications include peritoneal effusion or abscess formation, hemorrhage (inside abdominal cavity, inside digestive tract), ileus, anastomotic leakage, intestinal fistula, lymphatic leakage, gastroparesis, pancreatitis, lung infection, pleural effusion, urinary tract infection, renal failure, liver failure, cardio-cerebrovascular events (both lower extremities thrombosis, pulmonary embolism, myocardial infarction, arrhythmia, cerebral infarction, etc.), and others. Surgical complications will be evaluated in both groups. Complications will be reported and graded according to the Clavien-Dindo classification of surgical complications.

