### Data collection

Table 2 displays the schematic diagram for the timeline of patient assessment and data collection. Assessment on localization accuracy and safety will be performed by research physicians and recorded by the research nurse within 30-days after the laparoscopic colectomy. All information should be recorded in Case Report Form (CRF) in a timely, truthful and detailed manner. Researchers must input information into the CRF according to protocol requirements, and supervisors appointed by the research center will check the completeness and accuracy of the CRF and guide the research center personnel to make necessary modifications or additions. CRF will hand over data entry to a reliable medical data processor. Text items can only be checked manually after they are entered into the database from CRF. The data manager performs system checks on the information entered the database. Data will be locked upon completion of entry. Any subsequent changes to the database may only be made with the joint written consent of the clinical study leader, the study statistician, and the data manager.

**Table 2 Tab2:** Schematic diagram for the schedule of enrolment, interventions, and assessments

TIMEPOINT	STUDY PERIOD			
	Enrolment	Allocation	Post-allocation	
	−1 to −2 weeks	0	1 week	2 weeks
ENROLMENT:				
Eligibility screen	X			
Informed consent	X			
Allocation		X		
INTERVENTIONS:				
*Autologous blood*			X	
*Intraoperative colonoscopy*			X	
ASSESSMENTS:				
*Physical examination*	X		X	
*Laboratory tests*	X		X	
*Oncology assessment*	X			
*localization accuracy*			X	
*Surgical safety*				X

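### The serious adverse event definition omits life-threatening events and new admission or readmission, so some serious harms would not trigger the 24-hour ethics report

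*Protocol article*

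**What the plan says.** The Adverse events section does three things. It requires that every adverse event be captured: "Any adverse events will be recorded in detail on the CRF". It then defines the serious subset: "Events are defined as serious adverse events if leading to death, prolongation of hospitalization, permanent or severe disability, teratogenesis or carcinagensis, and significant clinical sequela". Finally, it requires serious events to be reported to the hospital's ethics committee "within 24 h of the initial discovery".

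Three other sections bear on the point:

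- **Intervention.** Conversion to open surgery is tied to "severe or life-threatening intraoperative complications such as intra-abdominal massive haemorrhage, severe organ damage", among other reasons. Life-threatening events are therefore foreseen, but only as grounds for conversion.
- **Secondary outcomes.** Tattooing harms are listed, "such as perforation, abscess formation, peritonitis, post-tattoo fever, post-tattoo abdominal pain, and intraperitoneal spillage of tattooing agent", followed by a long list of surgical complications that includes anastomotic leakage, pulmonary embolism and myocardial infarction. Complications are graded by Clavien-Dindo. No reporting duty is attached to any grade.
- **Data collection.** Accuracy and safety are assessed and recorded "within 30-days after the laparoscopic colectomy". Table 2 in the same section places the surgical safety assessment at 2 weeks.

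**The concern.** The definition decides which harms an outside body hears about quickly. Two grounds for seriousness are missing from it: that the event threatened life, and that it led to a new hospital admission. The only hospital-related criterion is a longer stay, which presupposes that the patient is already in hospital.

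Both gaps concern events that can occur in this trial. Major intraoperative bleeding is named in the protocol, and complications such as a leak or an abscess can appear after discharge while safety data are still being collected.

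At stake are prompt ethics oversight and a correct count of serious events. The 24-hour report is the only fast safety route the article describes. The other outside oversight it mentions is slower: annual monitoring by the funder, one interim analysis at half of randomisation, and annual progress reports to the funder and the ethics committee.

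**Working it through.** The protocol states no figure to reproduce. The check sets the definition against the rest of the document.

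**Step 1. Is the list closed?** It names death, longer hospital stay, permanent or severe disability, teratogenesis or carcinogenesis, and significant clinical sequela. It ends there. The sentence before it ends in an open-ended term, and so does the list of surgical complications under Secondary outcomes. The definition has none, so it reads as complete.

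**Step 2. Does another section fill the gap?** Intervention uses life-threatening complications only to trigger conversion. Secondary outcomes grades complications but links no grade to reporting. Data collection sets times and data handling. Roles and responsibilities assigns serious-event reporting to the investigators without redefining the term. None adds either criterion.

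**Step 3. Apply the rule as written.**

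| Event | Listed criterion met? | 24-hour report? | On CRF? |
|---|---|---|---|
| In-hospital leak that lengthens the stay | Yes, longer stay | Yes | Yes |
| Life-threatening intraoperative bleed, controlled, no longer stay, no sequela | None | No | Yes |
| Abscess or leak after discharge, readmitted, no sequela | None: a new admission is not a longer stay | No | Yes |
| Same readmission, with significant sequela | Yes, sequela | Yes | Yes |

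The second and third rows are the gap.

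**Step 4. Size.** The document gives no readmission rate, length of stay or rate of life-threatening events. Only a bound under an assumption is possible for readmissions:

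- Input from the protocol: 220 patients (110 per group).
- Assumption: 3% to 10% are readmitted during safety follow-up.
- Lower end: 220 × 0.03 = 6.6, about 7. Upper end: 220 × 0.10 = 22.

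So 7 to 22 readmissions would fail the hospitalisation criterion. This bounds the missed events from above, because each readmission that also meets death, disability or sequela is still reported. The document gives no basis for estimating that share. No figure can be given for life-threatening events that resolve.

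**The case against.** The strongest case against is that the gap is narrow and does no harm to the results. Much of that stands:

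- **Most grave in-hospital events are already covered.** A reader might infer that the gravest harms escape reporting. The documents do not support this. Death and permanent or severe disability are listed, and an in-hospital perforation, leak, peritonitis or embolism would usually qualify through a longer stay or significant sequela.
- **The bleeding example is not typical.** The Intervention section requires conversion to open surgery in such a case, and an on-time discharge after that is possible but hardly usual. The readmission example follows more directly from the wording.
- **Admission after tattooing is conditional.** One might add a patient tattooed as an outpatient and then admitted urgently. The article puts tattooing 24–48 hours before surgery but does not say whether patients are already in hospital, so the point cannot rest on that case.
- **No data are lost.** All adverse events reach the CRF, and surgical complications are graded in both arms. Neither the tattooing endpoint nor the Clavien-Dindo grading uses the serious label.
- **7 to 22 is not a count of missed events.** It rests on an assumed rate and is an upper bound.
- **The 30-day window is not firm**, since Table 2 gives 2 weeks for surgical safety.

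The objection does not remove the defect. The article states the definition in full and ties a reporting duty to it, so this is not a detail left to a longer document. CRF recording and yearly reports are not substitutes for notice within 24 hours.

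**Conclusion.** The point holds as a badly fixed safety-reporting rule with limited reach. The definition leaves out life-threatening events and new admission or readmission, and nothing else in the document supplies them. Two groups therefore miss the 24-hour report and any tally of serious events: life-threatening events that resolve with no longer stay and no sequela, and readmissions after discharge with no sequela.

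The size is unknown. The assumed 3–10% readmission rate gives a ceiling of 7 to 22 of 220 patients on the hospitalisation criterion, with the true number of unreported events lower by an amount the document does not allow one to estimate. The loss is of expedited notice and correct classification, not of data. The primary endpoint, non-inferiority margin, alpha, power and sample size are untouched.

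**What to change.** In the Adverse events section, add two criteria to the existing list: that the event is life-threatening, and that it requires hospital admission or readmission. Keep all current criteria. State that the definition applies in both arms, from the localisation procedure to the end of safety follow-up. Before fixing that end, reconcile the Data collection text (30 days after colectomy) with Table 2 (surgical safety at 2 weeks), so that the reporting period and the assessment schedule agree. Carry the same wording into the CRF.

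The cost is a sentence or two in the protocol and CRF, ethics committee approval of the amendment where required, and a few more expedited reports. No extra patients, visits or procedures are needed. The change should be made promptly, because a 24-hour report cannot be made in time for events that have already passed.
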